Therapists will send e-mails to the TG participants to encourage them to continue their efforts and they will be called if there is no response to these e-mails. Halfway through the program, their opinions about it will be sought (doubts, suggestions for improvement). This is intended to motivate the participants in order to improve adherence and minimize the risk of drop out.

The CG (waiting list) participants will receive a telephone call or e-mail informing them of the next program start date. In the event that during the study an individual (CG or TG) is found to have a worsening depressive mood (severe depression or suicidal ideation), the participant would discontinue the study and his or her physician would be notified in order to refer the individual to the Clinical Management Unit of Mental Health of the Andalusian Health Service.

Protocol amendments: Important protocol modifications will be reported to the researchers, the University of Malaga and the protocol registry.

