### Statistical analysis

First, a descriptive analysis will be conducted of the variables studied. For quantitative variables, measures of centralization and dispersion will be collected. For qualitative variables, a frequency analysis will be carried out.

To analyze cross-sectional and longitudinal differences, hypotheses will be contrasted at a 95% confidence level. To contrast differences between both groups (TG and CG) at baseline and post-treatment at a given time, Student’s *t*-test will be used (for strong violations of the normality assumption, the Mann-Whitney U-test) or analysis of variance (ANOVA). The effect size will be calculated using Cohen’s d.

To test whether the treatment produces differences over time (baseline, post-treatment, 3 months, 6 months and 12 months in the TG and baseline and post-treatment in the CG) in each of the groups, the *t*-test for related samples will be used (Wilcoxon signed-rank test in the event of strong violations of the normality assumption) or with an ANOVA for repeated variables and multiple regression model to control possible confounding variables (such as: age, gender, HbA1c, time with diabetes, etc.). For qualitative variables, McNemar’s test will be used.

To study the relationships between the different variables, Pearson’s correlation coefficient and linear regression models will be used for interval variables. The relationship between qualitative variables will be evaluated with the χ2 test.

Possible risk factors will be studied through logistic regression analysis (analysis of adherence to the treatment program).

The analyses will be carried out considering the subjects who complete the program. Analyses will also be carried out according to the protocol.

Analysis of the results will begin when the TG subjects have completed all of the phases of the treatment program. An improvement in the different variables will be taken into account in the following cases: significant differences in p≤0.05 and in the case of the BDI-FS when there is a decrease in the level of depressive symptomatology (moderate-mild, mild-minimum).

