### Sample size calculation

We calculated the effect size using Cohen’s [56] estimates for the calculation of sample size a priori. For this, the significance level was considered to be 0.05 and the power 0.80. Concerning the effect size, according to a recent review by Uchendu and Blake [14] on CBT in adults with diabetes, there is a moderate effect size (-0.43) in depression. Therefore, in our study, a moderate effect size (0.50) will be used. With these data, a sample size of 28 participants is needed. Since the study has 2 groups, 28 participants will be included in each of the groups (56 participants in total).

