We start from a treatment that is recognized as effective in the population in which it is to be applied [29–34] in depressive symptoms or depression and distress related to diabetes. However, no significant results were found regarding glycemic control, understood as the glycosylated hemoglobin (HbA1c) value. A possible explanation could be that, despite working with aspects related to the impact on the patient’s mood, changes in the treatment regimens for diabetes care are not directly addressed. This would make sense, as it is not the aim of this type of intervention. The study of other outcome variables of the web treatment on glycemic control, such as number of self-tests, episodes of hypoglycemia and hyperglycemia, and treatment adherence could add information along these lines. Moreover, other outcome variables with implications for treatment adherence, such as specific diabetes-related distress or fear of hypoglycemia, may also indicate structural changes that could influence long-term glycemic control. In addition, the number of sessions involved in treatment in previous studies has varied between 6 [32–36], 7 [37, 38] and 8 [29–31] treatment sessions. Based on previous studies and the existing relationships between depression and other variables in people with type 1 diabetes, in this study we have created 9 sessions.

Although it is known that adherence to Internet-based CBT treatment is lower than adherence when delivering the same treatment face to face [59], in the population with diabetes, there appears to be no difference between the two types of delivery [28]. Determining the variables involved in adherence to treatment will be among the data to be obtained in the present study. Accordingly, a comprehensive analysis of the medical and psychological variables involved in depression in people with diabetes, together with the variables that may affect adherence to this type of treatment in our study population, may help to provide greater insight into the effects of this treatment and the characteristics of the population in which it would be most beneficial (adherence), which are the main strengths of this study.

However, this study is not without limitations. The sample sizes of the previous studies are larger than the figure we aim to achieve in this study. Nevertheless, taking into account the rigor of the exclusion criteria and the sample size calculations described previously will enable reliable and valid conclusions to be drawn.

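### The 28 per group said to be needed is also the number enrolled, while the analysis is of programme completers, so the analysed sample is likely to fall short of a requirement that is itself too small

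*Protocol article*

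**What the plan says.** All references are to the protocol article.

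- **Sample size calculation.** The inputs are "the significance level was considered to be 0.05 and the power 0.80". A cited review is reported as showing that "there is a moderate effect size (-0.43) in depression", after which "a moderate effect size (0.50) will be used". The section concludes that 28 participants are needed, and continues: "Since the study has 2 groups, 28 participants will be included in each of the groups (56 participants in total"). No loss rate or inflation appears.
- **Statistical analysis.** "The analyses will be carried out considering the subjects who complete the program". The next sentence adds analyses according to the protocol. No analysis of everyone randomised is named. A logistic regression of adherence to the programme is also planned.
- **Intervention.** Therapists e-mail and telephone treatment-group participants and ask their opinions halfway through: "This is intended to motivate the participants in order to improve adherence and minimize the risk of drop out". Participants in either group whose mood worsens to a stated degree leave the study.
- **Discussion.** The sample size calculation is given as a reason to expect reliable and valid conclusions despite a sample smaller than those of earlier studies.

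**The concern.** A power calculation gives the number that must be analysed. Here the same figure serves as the number analysed and the number enrolled, so there is no margin: one non-completer takes the analysed sample below the stated need. The article also treats non-completion as something to expect, since it has measures to limit drop-out, a withdrawal rule, and a regression of adherence that can be fitted only if some participants do not adhere.

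What is at stake is how a null result would be read. A reader who takes the 0.80 at face value would treat a non-significant difference as fair evidence against a moderate effect. The trial would not support that reading, and the Discussion sentence would encourage it.

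**Working it through.** **Inputs from the article:** alpha 0.05, power 0.80, standardised effect 0.50, 28 per group, 1:1 allocation. For the comparison between groups the article names Student's t-test (Mann-Whitney under strong non-normality) or ANOVA.

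**Assumptions made here:** a two-sided test, because the article says only that "hypotheses will be contrasted at a 95% confidence level"; treatment-group loss of 10% to 40%, because the article gives no rate; and all 28 controls analysed at post-treatment, because they have not yet started the programme. One variant also loses controls.

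**Step 1. Try to reproduce 28 per group.** The normal approximation for two means gives

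n = 2(1.960 + 0.842)² / 0.50² = 2 × 7.85 / 0.25 = 62.8, so 63 per group.

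The exact t calculation gives 63.8, so 64 per group. One-sided, the figures are 50 and 51. With the review's 0.43 they are 85 and 86 two-sided. The figure of 28 per group is not reproduced for the two-group comparison. Numbers near 28 arise only under assumptions that the section does not state: a one-sided paired t-test (27), a repeated-measures ANOVA with three time points (28 in total), or a baseline-adjusted analysis with a correlation of about 0.75 (28 per group).

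**Step 2. Power with no loss.** The noncentrality is d√(n₁n₂/(n₁+n₂)) with n₁+n₂−2 degrees of freedom. For 28 v 28 it is 0.50 × √14 = 1.87 on 54 df, which gives 45% power. The effect detectable with 80% power is 0.76.

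**Step 3. Power with loss.** Treatment-group completers number 28 × (1 − loss) = 25.2, 22.4, 19.6 and 16.8, rounded to 25, 22, 20 and 17.

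| Analysed (treatment v control) | Noncentrality at d = 0.50 | Power at d = 0.50 | Effect detectable with 80% power |
|---|---|---|---|
| 28 v 28 (no loss) | 1.87 | 45% | 0.76 |
| 25 v 28 (about 10%) | 1.82 | 43% | 0.79 |
| 22 v 28 (about 20%) | 1.76 | 41% | 0.82 |
| 20 v 28 (about 30%) | 1.71 | 39% | 0.84 |
| 17 v 28 (about 40%) | 1.63 | 36% | 0.88 |
| 20 v 25 (controls also lost) | 1.67 | 37% | 0.86 |

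**Step 4. Enrolment needed to keep a given analysed number.** Enrolled = analysed / (1 − loss). To analyse 28 per group at 10%, 20%, 30% and 40% loss in each arm, enrol 32, 35, 40 and 47 per group. To analyse 64 per group, enrol 72, 80, 92 and 107.

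**The case against.** **Loss is possible, not certain.** A reader might infer that the analysed sample must fall below 28. The article does not support that. It gives no loss rate, the reminders and calls aim to limit drop-out, and the withdrawal rule is conditional. Strictly, at least one non-completer is needed. This stands, and the conclusion is only that a shortfall is likely.

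**The Discussion does not predict heavy loss.** It is tempting to cite "Although it is known that adherence to Internet-based CBT treatment is lower than adherence when delivering the same treatment face to face" as the article's own forecast. The sentence goes on to say that in people with diabetes there appears to be no difference between the two forms of delivery. It is therefore not evidence for loss here and is not used as such.

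**The completer rule does not fall equally on both arms.** Controls have not had the programme at the post-treatment comparison, so the restriction bears mainly on the treatment group, although controls can also withdraw. This stands. The sentence about analyses according to the protocol is unclear; read literally as per-protocol, it supplies no larger set.

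**Loss is not why 0.80 is missed.** A reader might infer that loss takes power from 80% to 68%. That drop appears only at an effect of 0.76, chosen backwards so that 28 v 28 gives 80%; the article plans for 0.50. At 0.50, power is already 45% without loss, and an assumed 10% to 30% treatment-group loss takes off about 2 to 6 points. This also stands: loss is the smaller part of one sizing problem.

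**An article condenses.** A retention assumption may be in the full protocol. That answers a complaint that a rate is missing. It does not answer the positive statements that 28 are needed, that 28 are included, and that completers are analysed.

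**Conclusion.** The point holds as a secondary part of the sizing error. The article sets the number needed equal to the number enrolled and then analyses completers, while anticipating drop-out, withdrawal and non-adherence. The analysed sample is likely, though not certain, to fall below the stated requirement, mainly in the treatment group at post-treatment.

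The 0.80 power is not delivered in any case, because 28 v 28 gives about 45% at the stated effect. Loss lowers this to between 43% and 36% and moves the detectable effect from 0.76 to between 0.79 and 0.88. These sizes rest on a two-sided t-test, an assumed loss of 10% to 40% in the treatment group, and complete follow-up of controls. The equality of needed and enrolled numbers would remain a fault after the 0.50 calculation is corrected, because any new requirement set equal to enrolment would again leave no margin for loss.

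**What to change.** In the sample size section:

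1. Separate the number enrolled (28 per group) from the number expected in the analysis.
2. State an assumed completion and retention rate for each arm, with its basis.
3. Correct the calculation for an effect of 0.50 and replace the 0.80 claim with the power, or the effect detectable with 80% power, at the expected analysed numbers. For example, 20 to 25 treated v 28 controls gives about 39% to 43% power at 0.50, or a detectable effect of 0.84 to 0.79. If a different test was meant to justify 28, name it and its assumptions.
4. Revise the Discussion sentence that relies on the calculation so that it matches.

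The cost is protocol wording and a few lines of calculation, and the stated power becomes less favourable. No extra enrolment is needed for this restatement. Inflating 28 for loss alone would not restore 80% power at 0.50. If the sponsor wants that power with this test, the enrolment figures based on 64 per group are the relevant ones.

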## Discussion

In this article, we present the design and methodology of the WEB_TDDI1 study, developed by our research group for the treatment of mild-moderate depressive symptoms in individuals with type 1 diabetes, with the aim of providing assistance to people experiencing this problem. An easily accessible platform has been created that includes 9 treatment sessions based on CBT, the experience of previous research in this population and the previous experience of pioneering authors of this type of Web therapy for people with diabetes [29–31].

Depression in individuals with diabetes is one of the issues associated with adherence, health outcomes and costs. Although screening of these patients is recommended to identify the presence of depression and prevent affected patients from going undetected so they may be correctly treated, screening does not always ensure that the patient wants to be treated [57]. In addition, the same study reported that once the screening period had ended the number of patients referred to mental health care decreased significantly [57] Burton et al. [58] found an increase in subjects treated after screening, but this increase was small [58] Therefore, treatment options that are familiar to the patient with diabetes and are flexible in their use could help increase the percentage of subjects who are treated once detected.

We start from a treatment that is recognized as effective in the population in which it is to be applied [29–34] in depressive symptoms or depression and distress related to diabetes. However, no significant results were found regarding glycemic control, understood as the glycosylated hemoglobin (HbA1c) value. A possible explanation could be that, despite working with aspects related to the impact on the patient’s mood, changes in the treatment regimens for diabetes care are not directly addressed. This would make sense, as it is not the aim of this type of intervention. The study of other outcome variables of the web treatment on glycemic control, such as number of self-tests, episodes of hypoglycemia and hyperglycemia, and treatment adherence could add information along these lines. Moreover, other outcome variables with implications for treatment adherence, such as specific diabetes-related distress or fear of hypoglycemia, may also indicate structural changes that could influence long-term glycemic control. In addition, the number of sessions involved in treatment in previous studies has varied between 6 [32–36], 7 [37, 38] and 8 [29–31] treatment sessions. Based on previous studies and the existing relationships between depression and other variables in people with type 1 diabetes, in this study we have created 9 sessions.

Although it is known that adherence to Internet-based CBT treatment is lower than adherence when delivering the same treatment face to face [59], in the population with diabetes, there appears to be no difference between the two types of delivery [28]. Determining the variables involved in adherence to treatment will be among the data to be obtained in the present study. Accordingly, a comprehensive analysis of the medical and psychological variables involved in depression in people with diabetes, together with the variables that may affect adherence to this type of treatment in our study population, may help to provide greater insight into the effects of this treatment and the characteristics of the population in which it would be most beneficial (adherence), which are the main strengths of this study.

However, this study is not without limitations. The sample sizes of the previous studies are larger than the figure we aim to achieve in this study. Nevertheless, taking into account the rigor of the exclusion criteria and the sample size calculations described previously will enable reliable and valid conclusions to be drawn.

## Conclusions

In this article, we present the design and methodology of the WEB_TDDI1 study, which includes a specific proposal for the treatment of mild-moderate depressive symptoms in adults with type 1 diabetes delivered through a Web-based CBT program. Based on previous studies, we anticipate an improvement in depressive symptomatology with respect to the control group and to baseline status, as well as an improvement in the secondary variables studied related to depression (anxiety, diabetes-related distress, fear of hypoglycemia, coping strategies, quality of life and adherence to diabetes treatment). Thus, this program is expected to provide professionals with a tool to treat mild to moderate depressive symptomatology in people with type 1 diabetes. Additionally, an analysis of the characteristics related to adherence to this program will be carried out to help establish profiles of people who will benefit from this type of treatment.
